## 11 Informed consent

The consent information will be delivered by the study nurse at the participating antenatal clinics, in a consulting room. Participants will have as long as they like to consider the information, although if they first present at 28 weeks gestation they will need to decide whether or not to participate during that week, as the study is integrated into the usual schedule of antenatal visits. Women who decide to join the study may withdraw at any time.

There will be three elements to consent for involvement; consent for eligibility screening; consent for inclusion in the trial; and consent for storage of blood samples.

Consent for screening will be sought from all women who appear potentially eligible at the pre-screening stage, and will be specific to procedures that are not normally undertaken as part of routine care. This includes a 5ml venous blood draw taken before enrolment, which will be used to assess the woman for anaemia, and, if the test has not already been undertaken, HIV and syphilis, as well as for study-specific tests if the woman is found eligible. It may also include an ultrasound scan, if available at this stage.

Informed consent for inclusion in the trial will be sought immediately before enrolment after 16 weeks gestation. Women who make first contact before 16 weeks and who are potentially eligible will receive all relevant information at this time, and will be asked for consent to screening, but will not be asked for their formal written consent for participation in the trial until their next attendance after 16 weeks.

Each potential participant will be given full and adequate oral and written information about the study, including all the known risks and any potential benefits, in their own local language. It will be clearly stated that the participant is free to withdraw from the study at any

time for any reason without prejudice to future care, and with no obligation to give the reason for withdrawal. Participants will be given the opportunity to ask questions and allowed time to consider the information provided.

Informed consent will be documented on a written consent form signed by the participant and the person who conducted the informed consent discussion. If the participant is unable to write her signature then a thumbprint may be used. If the subject is unable to read the information herself, full and comprehensive verbal information will be communicated in the presence of a witness; who will be independent of the conduct of the trial. The witness will sign the consent form to attest that information in the consent form was accurately explained and apparently understood by the participants, and that informed consent was freely given.

Participants will be asked for additional consent for the transport of blood sample outside of the country and the storage of blood samples for future research, and this consent will be recorded separately. Women who do not consent to the storage and transport of blood, or who withdraw their consent, can still participate in the trial.

Pregnant women aged 16 years or older are considered emancipated in Malawi and are able to sign the consent form for themselves; no parental consent is required for emancipated minors according to Malawian law.

Either carbon copies or otherwise two identical consent forms will be used per women; one signed or thumb-printed consent form will be kept on file by the study team and one given to the participant.

## **12 Data management**

Source documents will be the participants' antenatal cards, delivery and birth records, laboratory results, and clinic records. All study-relevant data will be transferred from the source documents to the case record forms (CRFs). In addition, some study specific data will be recorded directly onto the CRF. Each participant will have their own document file containing some of their original documents (e.g. print-out of automated laboratory results) and the CRF. The Principal Investigator will ensure that the CRFs are accurate, complete and legible.

The data recorded on the CRF will be input into an electronic database, managed by the data manager under the local PI in Malawi. Data validation and verification will be done to ensure that the data in the database corresponds with the CRFs and source documents. Data query sheets will be raised and distributed by the data manager to the study team for resolution in a timely manner. An anonymized, encrypted copy of the database will be kept at LSTM.

At the end of the trial and when the validation process is concluded and once all decisions on the evaluability of the data from each individual participant have been made and documented, the database will be locked.

All documents will be stored safely in confidential conditions. On all study-specific documents, other than the signed consent forms, the participant will be referred to by their unique study participant number and initials, not by name.

## 13 Withdrawal or discontinuation of study participants

Participants will only be withdrawn from the study for the following reasons:

- Withdrawal of consent by the participant. Participants may choose to withdraw at any stage.
- Screening failure. The participant did not meet the required inclusion or exclusion criteria, and was included in the study in error
- Loss to follow-up. The participant moved out of the study area, or was lost to follow-up for some other reason.
- Death of the study participant.
- Safety reasons as judged by the safety monitor, investigator or sponsor.

A participant who chooses to withdraw from the study will always be asked for her reasons and about the occurrence of any adverse events and the reasons for her withdrawal will be recorded on the CRF.

Participants who discontinue the study drugs will not be considered withdrawn from the trial. With the participant's consent, every effort will be made to follow up those who discontinue the study drug due to adverse events in order to determine the final outcomes.

Non-adherence to the study schedule will not lead to the withdrawal of the participant unless it indicates a significant risk to her safety.

Participants who discontinue the study prematurely will not be replaced.

## 14 Definition of end of trial

The end of trial will be defined as the final assessment of the last infant born within the trial, unless additional time is needed for follow-up of a trial-associated adverse event.

## 15 Treatment of trial participants

### 15.1 The study intervention

Participants will receive one of the following two interventions during the second and third trimesters of pregnancy; provided at each of three scheduled visits between four and six weeks apart.

**IPTp-SP Group:** Treatment with a three tablets of sulphadoxine-pyrimethamine, each containing sulphadoxine (500 mg) and pyrimethamine (25 mg). This is the standard and only

drug of choice for IPTp in Africa. SP will be purchased from Durbin PLC in the UK and will be manufactured according to the GMP: Durbin PLC is a UK registered company - Company Registration Number: 3626868; Head Office: [name] T: [name], F: [name], [contact]

**ISTp-DP Group:** Screening for malaria using a combined HRP-2/ pLDH (*P. falciparum*/ pan-malaria) rapid diagnostic test (First Response® Malaria pLDH/HRP2 Combo Test, target antigen pLDH (pan); HRP2; Premier Medical Corporation Ltd, USA), and treatment if RDT-positive with dihydroartemisinin-piperaquine (Sigma Tau). Each tablet will contain 40 mg dihydroartemisinin and 320 mg piperaquine. Treatment will be given for three days, with the daily number of tablets depending on the weight of the woman to the nearest half tablet; dosage being 2 mg/kg/day of dihydroartemisinin and 16 mg/kg/day piperaquine.

### 15.1.1 Administration of the study drugs

Women in either group who attend for a scheduled study appointment with fever and malaria confirmed by RDT or microscopy will be treated for malaria. In the case of women in the IPTp-SP group, case-management treatment will be given in place of the scheduled dose of SP, and this will be recorded on the CRF.

RDTs will be performed according to the manufacturer's instructions by the study staff at the clinic. Women in the ISTp group testing positive for either *P. falciparum* or other malaria species will be treated with DHA-PQ.

Participants receiving single-dose SP or the first dose of DHA-PQ will be given some clean water for swallowing the tablets. They will be observed swallowing the tablets and for thirty minutes afterwards. If vomiting occurs during this time the full dose will be repeated. If the participant vomits again after the repeated dose she will be discontinued from the trial and provided with second line therapy for malaria (CoArtem).

Participants receiving treatment with DHA-PQ will be given the remaining doses to take home, with instructions to take half the tablets the following day and half tablets the day after. Women with mobile or home telephones will be telephoned the next day to remind them to take their next dose. Women without mobile phone will be visited at home. All women regardless of mobile phone ownership will be visited by a fieldworker on the second day to check whether they have taken the tablets and whether they have had any problems.

## 15.2 Other treatment and concomitant medication

### 15.2.1. Routine care

All participants will be offered routine antenatal care according to local policy and the principles of 'focussed antenatal care'. This includes the provision of insecticide-treated bed nets (ITNs) free of charge.

Routine antenatal care in Malawi includes blood screening at the first appointment for syphilis, anaemia and HIV, and the provision of appropriate treatment for these conditions. Women diagnosed with anaemia or syphilis will be treated as appropriate. Women diagnosed before or during the trial as HIV-positive will be excluded or withdrawn from the

trial and offered co-trimoxazole prophylaxis. Blood screening for anaemia and HIV will also be repeated in the third trimester, as per usual care in Malawi (anaemia) and per new WHO guidelines (HIV).

As part of their antenatal care participants will be given iron and folic acid supplements (folic acid dose 0.4 mg to 0.6 mg / day) and tetanus vaccination if applicable. Helminth infections will be treated with praziquantel 40 mg / kg single dose for schistosomiasis infection, albendazole 400 mg / kg single dose for hookworm, trichuriasis and ascariasis, and albendazole 400 mg / kg per day for three days for strongyloidosis.

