### **15.2.2 Unscheduled visits**

Participants will be encouraged to attend the study clinics if they feel unwell, and will also be asked about their use of self-medications at each of their clinic appointments. All concomitant medications prescribed to participants during the study, or reported as used by the participants, will be recorded in the appropriate sections of the CRF with the indication, dose, and dates of administration.

Women diagnosed with symptomatic uncomplicated malaria during the course of the study will be treated with artemether-lumefantrine (CoArtem) as first line and with oral quinine as second line if they become symptomatic and parasitaemic again within 4 weeks. The exception is women in the ISTp group who are attending their first or other routine appointments, who will receive DHA-PQ if RDT-positive, with CoArtem reserved as second line therapy. Women with severe malaria will be admitted to hospital for treatment with intravenous quinine.

Study infants who become unwell at birth or during the follow-up period will also receive all appropriate healthcare as usually provided according to local policy and guidelines. Infants with severe jaundice will be treated with phototherapy according to national guidelines. Where umbilical cord blood is found to be positive for malaria by RDT at birth, microscopy smear of umbilical cord blood will be prioritised for the next 24 hours and, if positive, the baby will be treated for malaria according to national guidelines.

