#### 16.1.2 Baseline assessment

A baseline assessment will be conducted for each participant comprising demographic information, socioeconomic information, insecticide treated net (ITN) and indoor residual spraying use, medical and obstetric history, and clinical assessment. Any relevant information already collected during the screening process or at previous antenatal appointments for the same pregnancy will be copied from the antenatal cards onto the CRF, so that questions, tests and examinations are not unnecessarily duplicated.

Study-relevant information recorded at the first visit will include age; area of residence; prior use of ITNs; number of previous known pregnancies and number of previous births. Clinical assessment will include height and weight, fundal height, reported date of last menstrual period and estimated gestation.

A 5 ml venous blood sample will be taken and used for both routine and study-specific testing. This will be obtained after consent for eligibility screening has been obtained but before consent for enrolment in the trial; women who have not been tested for HIV in their current pregnancy will be tested for HIV, and all women will be tested for anaemia and haemoglobin levels. Women not previously tested for syphilis in this pregnancy will be tested and treated if positive. The same blood sample will be prepared for later study-specific testing for malaria (blood smear microscopy and PCR), for markers of immunity to *P. falciparum* malaria, and for markers of iron deficiency. Aliquots of separated blood plasma will be stored at -20 or -80C for immunity studies. A filter-paper sample will be prepared and stored for future research if the woman has given her consent for this.

If not already done, an ultrasound scan will be done at this visit or at a separate visit within a month of enrolment.

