#### **16.2.2 Routine antenatal care and treatment of illness**

Routine antenatal care and treatment of any illness identified at this visit will be provided as described in section 15.2.

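### Section 15.2.1 writes both albendazole doses as 400 mg per kilogram, which is 16 to 28 g per dose at assumed weights of 40 to 70 kg; the unit needs confirming and correcting

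*Combined protocol and SAP*

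**What the plan says.** Section 15.2.1 lists the treatments given as part of antenatal care. Its helminth sentence contains three doses:

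- "praziquantel 40 mg / kg single dose for schistosomiasis infection"
- "albendazole 400 mg / kg single dose for hookworm, trichuriasis and ascariasis"
- "albendazole 400 mg / kg per day for three days for strongyloidosis"

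The section opens by placing this within usual care: "All participants will be offered routine antenatal care according to local policy".

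The visit schedule then points back to it. For the interim visit, section 16.2.2 states: "Routine antenatal care and treatment of any illness identified at this visit will be provided as described in section 15.2". Sections 16.1.4 (booking visit) and 16.4.2 (final antenatal visit) make the same reference, and section 16.3 has the additional interim visit run in the same way as the interim visit.

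The protocol gives no other albendazole dose, and no maximum, tablet strength or weight band for it.

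**The concern.** Albendazole carries the same per-kilogram unit as praziquantel but a number ten times larger, and the result is a multi-gram dose. The likely explanation is that the unit was carried over from the praziquantel dose just before it.

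The protocol has other unit slips that make this credible. Anaemia is defined in g/dL in section 9.2.1, but in micrograms per litre in section 16.4.2 and in g/L in section 16.8.1. Section 9.2.1 also lists mean gestational age in grams. Unlike those, the albendazole entry is a dose to be given to pregnant women.

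The sentence is written as an instruction, in the section that the scheduled visits cite. Section 19 requires conduct according to the approved protocol. A clinician working from the text could therefore give a multi-gram dose, while one who gives a flat 400 mg departs from the protocol as written.

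**Working it through.** The plan states no total albendazole dose, so there is no figure of its own to reproduce. The check is dose per kilogram times body weight.

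**Inputs**

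- Albendazole, single dose: 400 mg/kg (section 15.2.1).
- Albendazole, strongyloidosis: 400 mg/kg per day for 3 days (section 15.2.1).
- Praziquantel: 40 mg/kg, single dose (section 15.2.1).
- Body weight: 40, 50 and 70 kg. These are assumptions. The protocol gives no participant weights; section 16.1.2 says only that weight is measured ("Clinical assessment will include height and weight, fundal height"). A per-kilogram dose could therefore be worked out in clinic.

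**Formulas**

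- Literal single dose = 400 mg/kg × weight.
- Literal three-day course = 3 × 400 mg/kg × weight.
- Praziquantel dose = 40 mg/kg × weight.
- Flat reading, with the per-kilogram unit removed = 400 mg once, or 3 × 400 mg = 1.2 g over three days.
- Literal dose divided by flat dose = (400 × weight) / 400 = weight in kg.

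**Results**

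| Assumed weight | Literal single dose | Literal three-day course | Praziquantel at 40 mg/kg | Flat 400 mg expressed per kg | Literal ÷ flat |
|---|---|---|---|---|---|
| 40 kg | 16 g | 48 g | 1.6 g | 10.0 mg/kg | 40 |
| 50 kg | 20 g | 60 g | 2.0 g | 8.0 mg/kg | 50 |
| 70 kg | 28 g | 84 g | 2.8 g | 5.7 mg/kg | 70 |

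The last column is simply the body weight in kilograms, so it adds no evidence beyond the unit itself.

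**Comparison with the other per-kilogram doses.** Section 15.1 gives dihydroartemisinin at 2 mg/kg/day and piperaquine at 16 mg/kg/day. The literal albendazole figure is 400/2 = 200 times the first, 400/16 = 25 times the second and 400/40 = 10 times the praziquantel figure. These are different drugs, so the ratios do not establish the correct albendazole dose. They show only that the written figure stands far apart from every other weight-based dose in the protocol.

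**The case against.** The documents contain no reference dose for albendazole. They cannot prove that 400 mg/kg is wrong or that a flat 400 mg was intended, and the 40- to 70-fold excess depends on that inference. This stands, and it is why the request is to confirm the unit before changing it.

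The route to harm is also weak. Care follows local policy, albendazole is not a study drug, and no helminth test appears in the visit schedule, the baseline assessment or the routine blood screening list. Nothing suggests that any woman was dosed per kilogram, and the number treated for helminths is not stated. These points stand too, and they make literal use unlikely. They do not correct the dose, and the sentence goes beyond a general reference to local policy by naming specific amounts.

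A faulty reading of the PDF is an unlikely explanation. The unit appears twice in the same form, in current protocol text.

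It can also be argued that searching past records is excessive for a probable clerical error. That would carry weight if new data had to be collected. However, section 15.2.2 already requires that concomitant medications "will be recorded in the appropriate sections of the CRF with the indication, dose, and dates of administration", so the search is a single listing.

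Finally, the point has no bearing on randomisation, endpoints, sample size or analysis. That is correct; it is a safety point about dosing text.

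**Conclusion.** The concern holds. Both albendazole doses in section 15.2.1 are written per kilogram, and nothing else in the protocol overrides them. At assumed weights of 40 to 70 kg, the text as written gives 16 to 28 g per dose and 48 to 84 g over three days. If a flat 400 mg was intended, that is 40 to 70 times too much.

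The wording and the arithmetic are certain. The body weights are assumed and the flat dose is inferred. The probability that anyone would follow the text literally is low but cannot be quantified from the documents. Because the possible consequence is a large overdose in pregnancy and the correction is simple, it should be fixed.

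**What to change.** 1. Have the sponsor's clinicians or pharmacist check the unit of both albendazole doses against the national guideline and the product information.
2. Correct section 15.2.1. The probable change is to remove the per-kilogram unit from both doses, leaving 400 mg as a single dose and 400 mg per day for three days, subject to that confirmation. The praziquantel dose is not in question here.
3. Send a note to all sites.
4. List any albendazole entries already in the concomitant-medication records and confirm that none was dosed per kilogram.

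The cost is a one-line amendment, a note to sites and one query of existing data. Section 22.2 requires amendments to go to the ethics committees before implementation, so that submission is also needed. Sample size, data collection and analysis do not change.

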### **15.2.2 Unscheduled visits**

Participants will be encouraged to attend the study clinics if they feel unwell, and will also be asked about their use of self-medications at each of their clinic appointments. All concomitant medications prescribed to participants during the study, or reported as used by the participants, will be recorded in the appropriate sections of the CRF with the indication, dose, and dates of administration.

Women diagnosed with symptomatic uncomplicated malaria during the course of the study will be treated with artemether-lumefantrine (CoArtem) as first line and with oral quinine as second line if they become symptomatic and parasitaemic again within 4 weeks. The exception is women in the ISTp group who are attending their first or other routine appointments, who will receive DHA-PQ if RDT-positive, with CoArtem reserved as second line therapy. Women with severe malaria will be admitted to hospital for treatment with intravenous quinine.

Study infants who become unwell at birth or during the follow-up period will also receive all appropriate healthcare as usually provided according to local policy and guidelines. Infants with severe jaundice will be treated with phototherapy according to national guidelines. Where umbilical cord blood is found to be positive for malaria by RDT at birth, microscopy smear of umbilical cord blood will be prioritised for the next 24 hours and, if positive, the baby will be treated for malaria according to national guidelines.

### **15.2.3 Prohibited medication**

Prohibited medication includes antimalarial drugs not prescribed within the trial protocol, and other drugs with antimalarial properties including co-trimoxazole. Participants who take prohibited medications will remain in the trial and will be included in the primary, intention to treat analysis, but excluded from the per-protocol analysis.

## **16 Schedule of visits**

### **16.1 Antenatal booking visit**

If a woman makes first contact with the study team between 16 and 28 weeks gestation, the first study visit will immediately follow eligibility screening. If a woman makes first contact before 16 weeks gestation it will be conducted at their next appointment between 16 and 28

weeks gestation. Informed consent will be obtained at this visit after completion of eligibility screening and before enrolment.

#### 16.1.1 Enrolment

After informed consent has been signed, participants will be randomly allocated (see section 17.2) to receive either IPTp or ISTp (see section 15.1) and issued with a trial identity card with their unique study identification number. Participants will be informed of study intervention they have been allocated to.

At this stage study staff will ask the participant for a home or mobile telephone number if they have one, and home address or a description of the location of their home, and for their verbal consent to be visited at home two days after receiving the study drugs (if they receive DHA-PQ) and whenever they do not attend scheduled appointments.

